### Researchers

2.6

The treatment will be performed by the same licensed acupuncturist with more than 6 years experience. In addition, 2 supervisory data collectors and analysts who do not know the random assignment protocol will monitor the whole experiment. People who are responsible for recruiting participants, researchers, outcome assessors, and the statistician in the trial will be trained before the trial strictly.

### Recruitment

2.7

The patients will be recruited mainly through the outpatient and inpatient areas of the rehabilitation center of the First Affiliated Hospital of Henan University of Traditional Chinese Medicine, and we will use the Internet for online recruitment. The poster will briefly describe the trial and provide treatment details and contact details to eligible participants, and contact information. Participants who are interested in participating will be able to contact the researcher directly.

We will provide the potential participants with a detailed description of the benefits of the trial and acupuncture and the risks that may exist. If they decide to participate, they will be asked to sign the informed consent. Then, they will be included in this trial for randomization. If a participant withdraws from the trial, the reasons for withdrawal will be recorded.

In order to improve the patients compliance in the trial, we will strengthen the doctor-patient communication and the patient's health education timely, to increase the patients’ trust in members of the research group.

### Safety assessment

2.8

Patient safety will be assessed in the whole process to avoid adverse events (AEs). All unpremeditated attacks and unexpected effects will be recorded on the AE Report Form. Treatment-related AEs include pain, haematoma, localized infection, broken needle, fainting, nausea, headache, dizziness, insomnia, or vomiting during or after treatment. Any serious adverse events (SAEs) will be immediately reported to the principal investigator and the Medical Ethics Committee within 24 hours. A primary investigation and follow-up monitoring will be performed if AEs are reported.

## Interventions

3

There are 3 groups in this trial, which are group A (*deqi* group), group B (without *deqi* group), and group C (waiting-list group).

The acupoints (Fig. 2) used in the trial include *Yanglingquan* (GB34), *Yinlingquan* (SP9), *Dubi* (ST35), and *Neixiyan* (EX-LE4). At the same time, depending on the patient's condition, 2 local acupuncture points can be added.

**Figure 2 F2:**
[figure not shown]
The picture of acupuncture points.

The acupuncture operation will be performed by the same licensed acupuncturist with more than 6 years experience, and will be trained in the clinical operation organized by the research group. Acupuncture treatment once a day, 5 sessions per week for 4 consecutive weeks, and rest for 2 days between treatments.

### Acupuncture with the deqi group

3.1

The specific operation method is as follows: after the patients in group A maintain a comfortable position, and the method of flattening and diarrhea is adopted. Then disinfect the skin with 75% alcohol, acupuncturist uses a sterile needle (0.25 mm in diameter, 40 mm in length, *Huatuo*, Suzhou, China) to the acupuncture points. Then, the needle is twisted between 90 and 180, lifted and thrusted in an even amplitude between 0.3 cm to 0.5 cm, 60 times to 90 times per minute. After the *deqi* sensation (including soreness, numbness, distention, and heaviness) is obtained, the needle will be retained for 30 minutes in each session and manipulated every 10 minutes with intermittent stimulation for maintaining the *deqi* sensation. The needle is totally used twice and the manipulation of each acupoint will last for 10 seconds. Table 1.

**Table 1 T1:**
[figure not shown]
Detailed information on acupuncture at each acupuncture point.

### Acupuncture without the deqi group

3.2

Subjects in the acupuncture without *deqi* group will undergo the same procedures as those in the acupuncture with *deqi* group. The needle depth is 1–2 mm and the needle will be directly retained for 30 minutes without any manipulation in the whole procedure to avoid the *deqi* sensation as much as possible (Table 1).

### Waiting-list group

3.3

Patients will not receive acupuncture treatment during the trial. These patients will be treated by acupuncture with *deqi* after finishing the trial.

If the patient has pain, bleeding, hematoma or other severe discomfort, the acupuncture treatment should be interrupted and treated immediately. During acupuncture treatment and follow-up, patients are prohibited from using drugs that treat knee osteoarthritis and relieve mood. If necessary, the details of the medication used and dosage of medication used should be recorded in the case report forms (CRFs).

## Outcome assessments

4

If only one knee is affected, the assessment of the outcomes will relate to this knee. If the patient has 2 affected knees of which only one meets the ACR criterion, only this knee will be evaluated. In the case that both knees are affected in accordance with the inclusion criteria (ACR), the more painful knee will be randomly chosen for evaluation.

### Primary outcome

4.1

We will use the Western Ontario and McMaster Universities Osteoarthritis Index (WOMAC) as the primary outcome measure.^[19]^ It consists of 24 items assessing the patients with KOA pain (5 items), stiffness (2 items) and physical function (17 items). The score ranges for the pain, stiffness and physical function subscales are, respectively, 0–50, 0–20 and 0–170, resulting in a total range of 0–240. Higher scores indicate more severe symptoms or physical disability. The evaluation will be performed at week 16 after randomization.

### Secondary outcome

4.2

#### Western Ontario and Mcmaster Universities Osteoarthritis Index (WOMAC)

4.2.1

The evaluation will be also performed at week 0, 4th, 8th, 12th, 20th, and 24th after randomization.

#### Knee injury and osteoarthritis outcome score (KOOS)^[20]^

4.2.2

The KOOS (Fig. 3) is self-assessed by the patient. The scoring system consists of 5 sub-domains with a total of 42 individual items. The 5 sub-domains are symptoms (7 items), pain (9 items), activities of daily living (17 items), entertainment and motor function (5 items), and quality of life associated with the knee joint (4 items). For each sub-scale, the outcome score will be normalized, where 0 indicates no symptoms and 10 indicates the most extreme symptoms. The evaluation will be performed at week 0, 4th, 8th, 12th, 16th, 20th, and 24th after randomization.

**Figure 3 F3:**
[figure not shown]
Study design schedule.

#### Arthritis quality of life measurement scale simplified scale (AIMS2-SF)^[21]^

4.2.3

Quality of life assessment using the AIMS2-SF Chinese version of the Arthritis Quality of Life Measurement Scale Simplified Scale by the Fudan University School of Public Health. The scale consists of 5 dimensions, 26 entries, of which 12 items of body (activity, walking, hand, arm, self-care), 3 items of symptoms (pain caused by arthritis), 5 items of emotion (the emotional impact of arthritis), social 4 items (social activities and social support) and work 2 items, because this test for KOA patients, the body dimension hand and arm a total of 5 items removed, a total of 21 items. All entries are scored on a scale of 1 to 5, and the total score is cumulatively represented by a score of 5 dimensions. The higher the score, the better the quality of life. The evaluation will be performed at week 0, 4th, 8th, 12th, 16th, 20th, and 24th after randomization.

#### Emotional monitoring

4.2.4

Mood changes, such as depression and anxiety, are common concomitant symptoms of KOA. The Beck Anxiety Inventory (BAI),^[22]^ and the Beck Depression Inventory (BDI)^[23]^ will be used in this trial to evaluate the emotional changes of patients in order to monitor the impact of emotional changes on the condition of KOA. The evaluation will be performed at week 0, 4th, 8th, 12th, 16th, 20th, and 24th after randomization.

#### Expectation scale

4.2.5

The treatment expectancy of participants will be evaluated by the Treatment Expectancy Questionnaire (1 = not at all, 5 = somewhat and 9 = very much), which has been transformed and translated into Chinese from the “Credibility and Expectancy Questionnaire”.^[24]^ Participants will be asked “How much do you feel acupuncture therapy will help to reduce your symptoms?” at the first visit.

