**Methods and analysis::**

A three-armed, parallel-design, randomized controlled trial is underway in China.108 KOA patients recruited by the rehabilitation center of the First Affiliated Hospital of Henan University of Traditional Chinese Medicine will be randomly assigned to the acupuncture with *deqi* group (A group), the acupuncture without *deqi* group (B group) and the waiting-list group (C group). Each patient will receive 5 30-minute sessions per week for 4 consecutive weeks and rest for 2 days between treatments, and undergo a 20-week follow-up. The primary outcome is the Western Ontario and McMaster Universities Osteoarthritis index (WOMAC score). The secondary outcomes include Western Ontario and McMaster Universities Osteoarthritis index (WOMAC score), Knee Injury and Osteoarthritis Outcome Score (KOOS), arthritis quality of life measurement scale simplified scale (AIMS2-SF), emotional monitoring and expectation scale. The pain visual analogue scale (VAS) and the Chinese version of modified Massachusetts General Hospital Acupuncture Sensation Scale (C-MMASS) will be used to evaluate the *deqi* sensation after each acupuncture treatment. At the same time, adverse events (AEs) occurred in the whole process will be recorded and analyzed. We will perform an intention-to-treat analysis and protocol (PP) analysis to statistically analyze the results of the trial.

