### Statistical analysis

4.6

In this trial, we will implement the intention-to-treat analysis and per-protocol (PP) analysis. The intention-to-treat analysis will be used for all allocated participants in the baseline. This trial focuses on the long-term effect of acupuncture, and the observed data will be used as the primary analysis. Primary analysis will be based on intention-to-treat population, including participants with at least 1 assessment of the primary outcome and 1 acupuncture session. Per protocol (PP) analysis will be performed to test the robustness of the primary analysis. PP population will include participants receiving at least 12 sessions of acupuncture and be assessed at week 16.

The demographic and baseline characteristics among 3 groups will be compared using one-way analysis of variance (ANOVA). A χ^2^ test will be used for categorical variables. Due to the occurrence of self-healing tendency in KOA, it is important to testify the existence of the long-term effect of acupuncture effect. The clinical outcomes will be compared among the acupuncture with the *deqi* group, acupuncture without the *deqi* group and the waiting treatment group at every time points (week 0, 4th, 8th, 12th, 16th, 20th, and 24th after randomization) by using the repeated measures ANOVA (3 independent groups with repeated measures).

Clinical outcomes will be analyzed using SPSS 22.0 statistics software (IBM SPSS Statistics, IBM Corp, Somers, NY, USA). Data on Skewed distribution will be normalized. Means, standard deviations, and 95% confidence intervals (CIs) will be used to describe the continuous data. All statistical hypotheses are two-sided tests, and the significance test level α = 0.05, giving the test statistic and its corresponding *P* value, with *P* ≤ .05 as statistically significant. The data will be analyzed by statisticians who are blinded to the test settings. All confidence intervals will be two-sided 95% intervals among the 3 groups (group A, group B and group C).

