The randomized controlled study design is an in-depth study of reliable methods based on the long-term analgesic effect of acupuncture. At the same time, it is a randomized controlled study that is an important source of high-quality evidence-based medical evidence for acupuncture. In the trial, we take acupuncture without *deqi* group as the control group. It is often regarded as a sham control group, because its acupuncture depth is only broken and does not reach the anatomical layer of the acupuncture point. Studies^[42–44]^ have shown that the placebo effect of sham acupuncture is more pronounced than drug-based placebo, especially for subjective outcomes and pain management. Therefore, our study has set a sham acupuncture group to eliminate the effects of placebo effects and patients’ expectations. And in the idea of acupuncture treatment of knee osteoarthritis, local acupoints have been used since ancient times. “*Su Wen*” says, local *Ashi* Point for the treatment of knee pain. A number of modern clinical studies^[44,45]^ have shown that local acupoints are widely used in the treatment of KOA by acupuncture, and the curative effect is remarkable. Some researchers^[45]^ used data mining to analyze the relevant literature of modern acupuncture treatment for KOA, and found that *Dubi*, *Neixiyan* and *Yanglingquan* were the top 3 acupoints with the high frequency. Another study^[46]^ shows that *Ashi* point is also one of the high-frequency acupoints. Thus, this study will select *Dubi*, *Neixiyan* and *Yanglingquan*, *Yinlingquan* as the acupuncture points. At the same time, depending on the patient's condition, 2 local acupuncture points can be added.

In order to improve the reliability of the study data, we carry out quality control from the following aspects:

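### The expectation scale is listed as a secondary outcome but is asked once, at the first visit, so it cannot show a treatment effect or enter the week 0 to 24 comparison, and its order relative to arm disclosure is not stated

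*Protocol article*

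**What the plan says.** The abstract's list of secondary outcomes ends with "emotional monitoring and expectation scale". In the body, the scale is section 4.2.5, under the heading Secondary outcome. It is scored from 1 to 9, and the text gives one question and one occasion: "Participants will be asked “How much do you feel acupuncture therapy will help to reduce your symptoms?” at the first visit".

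The other secondary outcomes have a follow-up schedule. For the anxiety and depression inventories, section 4.2.4 says: "The evaluation will be performed at week 0, 4th, 8th, 12th, 16th, 20th, and 24th after randomization". KOOS and AIMS2-SF have the same seven time points. WOMAC has six of them as a secondary outcome, and week 16 is the primary assessment (sections 4.1 and 4.2.1).

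Section 4.6 compares the clinical outcomes of the three arms "at every time points (week 0, 4th, 8th, 12th, 16th, 20th, and 24th after randomization) by using the repeated measures ANOVA". It names no covariate. It also plans a check at entry: "The demographic and baseline characteristics among 3 groups will be compared using one-way analysis of variance (ANOVA".

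Two other sections bear on timing. Under section 2.5, patients and the acupuncturist are not blinded. Under section 2.4, the acupuncturist learns the allocation by telephone 5 to 10 minutes before treatment.

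**The concern.** A secondary efficacy outcome should be able to respond to treatment. A score taken once, at the start, cannot reflect what a 4-week course did. Calling it an outcome sets up a secondary result that the schedule cannot supply, and the only general method stated for clinical outcomes needs repeated values that do not exist for this scale.

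The order of events is a second problem. Patients know their arm, and the waiting-list arm receives no acupuncture during the trial (section 3.3). Expectation recorded before disclosure is a clean baseline characteristic. Recorded after disclosure, it may partly reflect the allocation itself. Its proper use in any analysis depends on which applies.

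The protocol treats expectation as important. Section 5 says of the shallow-needling arm that "our study has set a sham acupuncture group to eliminate the effects of placebo effects and patients’ expectations". The one direct measurement of expectation should therefore have a status and timing that let it be used.

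**Working it through.** The plan gives no figure for this scale. The sample size in section 2.3 rests on the WOMAC total score and is unaffected. The check sets the measurement schedule against the planned analysis.

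**1. Measurements against planned time points**

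| Measure | Stated assessments | After week 0 |
|---|---|---|
| WOMAC (primary and secondary together) | 0, 4, 8, 12, 16, 20, 24 | 6 |
| KOOS, AIMS2-SF, BAI, BDI | 0, 4, 8, 12, 16, 20, 24 | 6 |
| Expectation scale | first visit only | 0 |

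Taking the first visit as week 0, coverage is 1/7 = 14% of the time points and 0/6 of those after baseline. With one value per patient there is no within-patient factor, so a repeated measures ANOVA cannot be fitted to this scale. With no value after treatment starts, no treatment effect on it can be estimated.

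**2. What a comparison of the arms would mean**

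- Asked before the arm is known: any difference among randomised arms is chance. A test at the 0.05 level would be positive about 5% of the time and would describe baseline balance only.
- Asked after the arm is known: a difference could also be a reaction to the allocation. The 5% figure no longer applies, and the score is not a valid baseline covariate.

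The text of section 4.2.5 does not say which case holds. The schedule in Figure 3 was not readable in the version reviewed, so this statement concerns the text only.

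**3. What adjustment could gain**

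Let r be the partial correlation of expectation with week-16 WOMAC, given arm and baseline WOMAC. Adding expectation multiplies the residual variance by about 1 − r² and the standard error by about √(1 − r²). The document gives no r. Values of 0.2 and 0.4 are assumed here for illustration:

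- r = 0.2: r² = 0.04 and √0.96 = 0.980, so the standard error falls by about 2%.
- r = 0.4: r² = 0.16 and √0.84 = 0.917, so the standard error falls by about 8%.

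**4. What adjustment costs**

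With 99 evaluable patients and 3 arms, a week-16 comparison has 99 − 3 = 96 residual degrees of freedom. Two covariates (baseline WOMAC and expectation) leave 94.

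**The case against.** The strongest reply is that section 4.6 never names the expectation scale. It applies the repeated measures ANOVA to clinical outcomes and separately plans a baseline comparison, which is a natural place for a first-visit score. No sentence promises a between-arm expectation result after treatment. On this reading the fault is one of labelling. That largely stands. It does not rescue the label: the abstract and section 4.2 still call the scale a secondary outcome, and an unseen analysis plan cannot supply later values that the stated schedule does not collect.

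A reader might also infer stronger points that the documents do not support:

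- **That covariate adjustment is the only possible use of the score.** It could equally describe the sample, check that the arms are comparable, or be examined as an effect modifier.
- **That leaving it out as a covariate is an error.** The article names no covariate for any outcome, and this choice is commonly left to the analysis plan. The remark in section 5 concerns the choice of control arm and promises no statistical adjustment.
- **That without adjustment the week-16 comparison is biased.** Chance imbalance under randomisation is already allowed for in the nominal error rate. Adjustment would improve precision.
- **That the score is certainly a pre-allocation value.** A value from before treatment is a fair reading of the text, but a value from before allocation is not stated.

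**Conclusion.** The inconsistency is real and limited in reach. As scheduled in the text, the expectation scale has no post-treatment value. It therefore cannot serve as a secondary outcome and does not fit the comparison over weeks 0 to 24. This follows from the schedule alone and needs no assumption beyond reading the first visit as the start of the trial.

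The open order of questioning and arm disclosure matters as well, because patients are unblinded and the score is a valid baseline variable only if it comes first.

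The covariate point is a recommendation. Its benefit cannot be sized from the document: the 2% to 8% reduction in standard error rests wholly on an assumed partial correlation of 0.2 to 0.4. The primary outcome, its week-16 time point, the sample size and the validity of the primary inference do not depend on this point.

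**What to change.** 1. In the abstract and section 4.2.5, move the expectation scale from the secondary outcomes to the baseline measures.
2. In section 4.2.5, state that the question is put before the arm is disclosed to the patient. Recruitment began on March 1, 2020 (section 6), so also record the order actually used for patients already enrolled. If some were asked after disclosure, report their scores descriptively and do not use them as baseline values.
3. In section 4.6, state that the scale is not part of the repeated measures comparison.
4. Pre-specify baseline WOMAC and expectation as covariates in the week-16 WOMAC comparison, or keep expectation for a named supporting model.

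Steps 1 to 3 are wording changes, plus a fixed order of questioning at the first visit. Step 4 uses data already collected and costs about one degree of freedom per covariate. The trial loses one nominal secondary outcome. If the sponsor does want expectation as an outcome, later assessments would have to be added, which means new data collection.

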### Evaluation indexes of *deq*i

4.3

Before the acupuncture treatment, each patient will be introduced with the concept of *deqi* and the sensation of *deqi*. Participants in the acupuncture with the *deqi* group and acupuncture without the *deqi* group will be asked to fill the needle sensation evaluation form after receiving each acupuncture treatment.

#### The pain visual analogue scale (VAS)^[25]^

4.3.1

The VAS scale is used to quantitatively evaluate the sensation of aspiration after the acupuncture treatment. The intensities of these sensations are evaluated on a 0 to 100 mm VAS, where 0 represents “none” and 100 represents “intolerable strong sense”. The participant will mark a point on the horizontal line according to the feeling of self, indicating the degree of pain. In addition, if the scale does not fully describe the acupuncture sensation experienced by the subject, the subject can add their sensation in a blank line below the scale.

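### Section 4.3.1 contradicts itself on whether the VAS listed as a deqi index rates pain or the strength of the needling sensation

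*Protocol article*

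**What the plan says.** The abstract names the pain VAS together with the C-MMASS as the measures of deqi: "Acupuncture Sensation Scale (C-MMASS) will be used to evaluate the *deqi* sensation after each acupuncture treatment". Section 4.3 lists both as evaluation indexes of deqi. Patients in groups A and B are first told what deqi is, and they "will be asked to fill the needle sensation evaluation form after receiving each acupuncture treatment".

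Section 4.3.1 then describes the VAS. The heading calls it a pain scale. The text says that it quantifies the sensation after needling and rates the intensity of several sensations from 0 to 100 mm, "where 0 represents “none” and 100 represents “intolerable strong sense". The next sentence tells the patient what the mark means: "The participant will mark a point on the horizontal line according to the feeling of self, indicating the degree of pain". A blank line lets patients add any acupuncture sensation that the scale does not cover.

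Elsewhere, section 3.1 describes deqi as "including soreness, numbness, distention, and heaviness". Section 3.2 has the needle in group B retained "without any manipulation in the whole procedure to avoid the *deqi* sensation as much as possible". Section 2.8 lists pain first among treatment-related adverse events: "Treatment-related AEs include pain, haematoma, localized infection, broken needle, fainting".

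**The concern.** The trial asks whether deqi influences the long-term effect of acupuncture, so the A-versus-B comparison can be read that way only if the two arms did differ in deqi. The protocol names two instruments that can show this, and one of them has an instruction that asks for something else. Patients and the acupuncturist are unblinded (section 2.5), which makes direct evidence on the sensation itself more valuable.

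A single line whose anchors say sensation and whose instruction says pain can be marked either way by different patients, or by the same patient at different sessions. Scores collected like that have no single meaning. A higher VAS in group A might be deqi or might be discomfort from manipulation. Similar scores in A and B might hide a real difference in deqi.

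**Working it through.** No figure in the protocol is in dispute, so the check sets the statements side by side.

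**What each part of section 4.3.1 says the line measures**

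- Heading (and the scale's name in the abstract): pain.
- Placement under section 4.3: deqi.
- Purpose sentence: the sensation after needling. The noun used looks mistranslated, but the section heading points to deqi.
- Rating sentence and its anchors: intensity of sensations, from none to intolerably strong, with no mention of pain.
- Marking instruction: pain.
- Free-text line: acupuncture sensation.

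The heading and the instruction point to pain. The purpose, the rating sentence with its anchors, and the free-text line point to sensation. The instruction is the only sentence that says what the mark indicates, so the majority of the text does not simply override it.

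**What follows under each reading**

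1. Sensation reading: the score is a global rating of needling sensation, usable as a supporting deqi index. Nothing is lost.
2. Pain reading: the score is needling pain. In group A the needle is twisted, and lifted and thrust over 0.3 to 0.5 cm (3 to 5 mm). In group B it sits at 1–2 mm without manipulation. Needling in A is therefore deeper and more active, and could plausibly hurt more for that reason alone. An A-versus-B difference could not then be credited to deqi. A patient with marked heaviness or numbness and no pain would be under-scored.
3. Mixed reading across patients: the mean has no defined construct.

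**Whether the deqi check survives without the VAS**

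Section 3.1 lists four sensations. Against the 11 rated by the C-MMASS in section 4.3.2: soreness appears, numbness appears, heaviness appears, and distention appears as fullness/distension. That is 4 of 4. The C-MMASS is completed at the end of each treatment, so the A-versus-B deqi contrast can still be tested.

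**What depends on the VAS**

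- Primary outcome (section 4.1): WOMAC at week 16. No dependence.
- Analysis populations (section 4.6): defined by assessments and sessions attended. No dependence.
- Sample size (section 2.3): based on reductions in WOMAC total score. No dependence.

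**Upper limit on ratings involved**

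108 / 3 = 36 patients per arm. Two needled arms × 36 patients × 20 sessions = 1,440 ratings, with full attendance and no dropout. This counts forms; it does not estimate how many are wrong.

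**The case against.** The strongest reply is that most of section 4.3.1 describes strength of sensation, and that the pain wording may be a slip of translation in an article whose English is uneven in other places. The form that patients complete is not shown and may ask the right question. Section 4.3 also says that patients are introduced to deqi beforehand, which would steer them towards rating it. This stands to the extent that the text does not establish that the VAS scores pain. It does not remove the conflict, because an introduction to deqi does not cancel an instruction to mark pain.

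A second reply is that the protocol does not keep pain and deqi strictly apart. The list in section 3.1 is introduced as non-exhaustive, and the C-MMASS counts aching and dull pain among its 11 sensations. Listing pain as an adverse event in section 2.8 does not define deqi either. This also stands. Some pain-like sensation may belong to deqi, but the degree of pain is still not the same quantity as the intensity of soreness, numbness, distention and heaviness.

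A reader might go further and infer that the trial cannot show that the arms differed in deqi, or that any week-16 difference would be misattributed. The documents do not support that. It would apply at most to the VAS, only under the pain reading, and the C-MMASS covers the gap. Nor do they support a claim that individual scores are wrong across the whole 0 to 100 range. That would need the form and data on how patients marked it.

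**Conclusion.** The point holds as an internal contradiction about what one of the two deqi indexes measures. Followed as written, the VAS has no single meaning, and an A-versus-B difference on it could be needling pain. It is worth correcting because the trial is about deqi, is recruiting according to section 6, and the change is small.

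The consequence is limited to the check that the arms differed in deqi, and within that check to the VAS. The size of any distortion cannot be given from the documents; 1,440 ratings is only the ceiling. The harm described assumes that the form carries the pain instruction and that at least some patients follow it. If the form asks for strength of sensation, the matter reduces to a wording error in the article and the ratings are sound.

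**What to change.** 1. In section 4.3.1 and the abstract, drop the word pain from the name of the scale. Replace the instruction to mark the degree of pain with one to mark the intensity of the deqi sensation as described in section 3.1. The existing anchors can stay.
2. Check the form in use. If it asks for strength of sensation, correct the article only and keep all ratings.
3. Only if the form carried the pain wording: correct it, do not analyse the ratings already collected as deqi, and rest the A-versus-B deqi check on the C-MMASS. If needling pain is wanted for its own sake, a separate labelled line would serve, but that is optional.

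The cost is an amended sentence, a renamed scale and possibly a reprinted one-line form. The downside is that any forms completed under the pain wording could not be pooled with later ones. Treatment, visits, the primary analysis and the sample size do not change.
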